## Abstract

**Background:**

The organization of long-term care is one of the main challenges of public health and health policies in Europe and worldwide, especially in terms of care concepts for people with dementia. In Austria and the Czech Republic the majority of elderly institutionalized persons with dementia are cared for in nursing homes. It is however unclear, how many persons living in nursing homes in Austria and in the Czech Republic are suffering from cognitive impairment and dementia. In addition, basic information on the nutritional status, the status of mobility and the medication prescription patterns are often missing. To facilitate new effective and evidenced based care concepts, basic epidemiological data are in urgent need. Thus, DEMDATA was initiated to provide important basic data on persons living in nursing homes in Austria and the Czech Republic for future care planning.

**Methods:**

DEMDATA is a multicentre mixed methods cross-sectional study. Stratified and randomly drawn nursing homes in Austria and the Czech Republic are surveyed. The study protocol used in both study centres assesses four different domains: a) Resident, b) Care team, c) Relative and d) Environmental Factors. Resident’s data include among others health status, cognition, dementia, mobility, nutrition, behavioural symptoms, pain intensity and quality of life. A minimum of 500 residents per country are included into the study (*N* = 1000 residents). The care team is asked about the use of the person-centred care and their burden. The relatives are asked about the number of visits and proxy-rate the quality of life of their family member. All staff employed in the nursing homes, all residents and relatives can voluntary take part in the study. The environmental factors include among others the organisational category of the nursing home, number of residents, number of rooms, social activities and the care concept. The project started in March 2016 and will be concluded in February 2018.

**Discussion:**

DEMDATA will provide important epidemiological data on four different nursing home domains in Austria and the Czech Republic, with a focus on the prevalence of dementia in this population. Thereby supplying decision and policy makers with important foundation for future care planning.

## Background

There are currently 46,8 million persons living with dementia worldwide [1]. Alzheimer Europe estimates that there are currently 145.431 persons with dementia living in Austria and 143.309 in the Czech Republic [2]. A rapid and continuous growth in an aging population [3] suggests that these numbers will double every 20 years [1]. This also entails an increase in persons living in nursing homes. Even though, there is a political plan to increase community care over institutional care, [4] the need for institutional Long term Care (iLTC) will remain over the next years. The organization of long-term care (LTC) including iLTC is one of the main challenges of public health and health policies in Europe [5–7] and worldwide [1], especially in terms of care concepts for people with dementia [8, 9]. The majority of elderly institutionalized persons from Austria and the Czech Republic with dementia living in iLTC are cared for in nursing homes. It is unclear however, how many persons living in nursing homes in Austria and in the Czech Republic are suffering from cognitive impairment and dementia. Studies conducted in other European countries produced diverse prevalence results. For example, in a large Swedish Study with 4831 studied nursing home residents, the prevalence of cognitive impairment was 67% [10]. In another study performed in nursing homes in Ireland, 58% percent had a dementia diagnosis. 31.8% had no medical dementia diagnosis but scored in clinical tests within the range of possible dementia, resulting in a total prevalence of 89.8% [8]. Considering the low diagnosis rate in some Austrian regions for home dwelling persons with dementia, the percentage of undiagnosed persons living in Austrian nursing homes may even be higher in some Austrian institutions [11]. Since an appropriate diagnosis is necessary for attending to the special medical and health care needs of this population, [9, 12] there is an urgent need for basic epidemiological data. The substantial increase of persons with dementia in nursing homes and the increased awareness of the needs of persons with dementia raises several challenges and requires either adaptations to current care practices or the development of alternative care concepts. Various approaches, most of them based on the concept of person-centred care [13] have been considered, but no convincing advantages of one care model over another could be found so far [14–16]. The results of different studies suggest a multifactorial approach to the development of specialized care models for persons with dementia, taking needs of residents, care teams and family members as well as environmental and psychosocial factors into account [17, 18]. The complex care needs associated with dementia in the different disease stages [10] lead to a higher care dependency, resulting in an increased stress and burden level in care teams [4, 19–21]. Testad et al. [22] found a positive correlation between behavioural symptoms and staff burden. A study in the Netherlands demonstrated how behavioural symptoms correlate with multiple environmental and social factors such as number of persons living in a unit, staff/patient ratio, the presence of a walking area and possibilities of social contact [23]. There is growing evidence that, even among those working in specialist dementia services, the proportion of staff receiving dementia care training is low [24–26]. Although dementia is an important topic in elderly long- term care, there are other important issues, such as infections [27] falls [28], pain management [29, 30] and the health status in general. There is also little knowledge on the potential for the improvement of medical services and the application of non-pharmacological therapies. The therapeutic nihilism in these environments is known to a certain extent but the potential has rarely been explored [31]. The lack of reliable information on these issues, as well as factors influencing the burden and stress of the care team is hindering the development of new innovative and cost effective care concepts [4].

DEMDATA was initiated to provide important basic data on persons with dementia living in nursing homes in Austria and the Czech Republic for future care planning. The goal of DEMDATA is to collect epidemiological data on four domains: a) Resident, b) Care team, c) Relative and d) Environmental Factors. This paper describes the main components of the DEMDATA study design, the study protocol for the quantitative data collection and the data management plan. The protocol for the qualitative data collection process will be described in a separate publication.

## Methods/Design

### Study design

DEMDATA is a multicentre mixed methods cross-sectional study. Stratified and randomly drawn nursing homes in Austria and the Czech Republic are surveyed. The project started in March 2016 and will end in February 2018. A minimum of 500 residents per country are included into the study (Total *N* = 1000 residents). This number has been estimated as a representative sample, as the population of nursing homes is relatively homogenous compared to community dwelling populations. The project is divided into four main study phases: Phase 1: Development and piloting of a common study protocol, Phase 2: Quantitative Data collection, Phase 3: Qualitative data collection, Phase 4: Analysis of data and publication of results.

A common working definition for the term ‘nursing home’ was agreed upon, as cross-country differences in institutionalized elderly care and different ideas on what necessary features constitute a nursing home exist. According to Sanford et al. [32], nursing homes are characterized by the following five parameters: (1) provides 24-h functional support for people who require assistance with activities of daily living (ADL)/instrumental activities of daily living (IADL) and have identified health needs; (2) may or may not be staffed with health care professionals; (3) provides long term care and/or rehabilitation as part of hospital avoidance or facilitate early hospital discharge; (4) does not function as a hospital ward and is not hospital based; (5) may play a role in providing palliative and/or hospice care at end of life.

There are currently 886 nursing homes in Austria and 822 in the Czech Republic. In Austria, there are three categories of nursing homes: (1) Homes under the administration of the federal state. In Upper Austria, these homes are managed by a commissioned organisation called *Sozialhilfeverband* (Social Help Organisation), (2) Homes under the administration of the municipality and (3) private homes of religious organizations or for profit organizations. To be admitted to a nursing home in Austria, a person needs to have a minimum level of care. The Austrian care system has seven levels of care. Each care level is defined by hours of care per month and person. Potential nursing home residents need to be ranked at a minimum level of 3, which is defined as: a person needing at least a care effort of 120 h/month.

There are 2 categories of nursing homes in the Czech Republic: a) Homes for seniors and b) Homes with a special regime. Each of these can be further organised in 3 categories: 1) Homes under the administration of the municipality, 2) private homes under the administration of for profit organizations, and 3) homes under the administration of non-governmental or religious organisations (Non-profit).

In order to minimize travel expenses for the research staff, three geographical areas for data collection were selected. In Austria, the federal state of Upper Austria with an area of 11.979,91 km^2^ and 1.453.733 inhabitants was selected. For the Czech Republic, the federal state Central Bohemia and Prague were selected. Central Bohemia has an area of 11.014,97 km^2^ and 1.291.816 inhabitants, Prague has an area of 496 km^2^ and 1.267.449 inhabitants.

According to an official list of the federal state of Upper Austria, 137 nursing homes are currently registered in Upper Austria. 159 nursing homes are registered in Central Bohemia and the Prague region.

Inclusion criteria for the residents are permanently living in the selected nursing home (independently of the length of stay) and a signed informed consent. All residents who have an acute health crisis (i.e. intensive care) or are in the process of dying will be excluded from the study. All care team members, administrative employees of the nursing homes, as well as relatives of the residents take part in the study on a voluntarily basis.

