### Sampling procedure

#### Austria

The 137 nursing homes of Upper Austria (from a total of 886 nursing home in Austria) formed the basis for the Austrian randomized selection process (see Fig. 1)﻿. Nine homes had to be excluded from the study, because they were “under renovation”. The remaining Austrian sample of 128 nursing homes includes facilities with 60–120 residents. From the remaining 128 homes, 82 nursing homes are run by the federal state, 21 are under municipal administration and 25 are organized by the church or private organizations. Each nursing home was assigned an identification number (ID). All numbers were written on separate pieces of paper and folded, concealing the ID number. The folded papers where then placed in different bowls representing the three organisational categories. Taking the drop outs into consideration, 16 nursing homes were randomly selected in a stratified fashion from the bowls (50% federal state; 25% municipality, 25% church/private). With this method, 16 nursing homes (8 federal state homes, and 4 municipal homes and 4 privately run homes) were randomly drawn. Of these 16 homes, seven nursing homes (five nursing homes run by the federal state, one home run by municipality and one home run by the church) consented to participate. In total, 644 residents are included in the Austrian sample.

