## Discussion

DEMDATA will provide important epidemiological data on four different nursing home domains (resident, care team, relative and environmental factors) in Austria and the Czech Republic. A special focus is put on the prevalence of dementia in this nursing home population. If additional funding is granted, the data produced within this project will be prepared for data sharing and be made openly available in an anonymized fashion.

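### Dementia prevalence is measured only in residents with a signed consent, so it may misstate prevalence among all residents if enrolment depends on dementia

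*Protocol article*

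**What the plan says.** All references are to the protocol article.

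- **Entry (Study design):** "Inclusion criteria for the residents are permanently living in the selected nursing home (independently of the length of stay) and a signed informed consent". The shown text does not say who may sign. The abstract adds that taking part is voluntary: "All staff employed in the nursing homes, all residents and relatives can voluntary take part in the study".
- **Exclusions (Study design):** "All residents who have an acute health crisis (i.e. intensive care) or are in the process of dying will be excluded from the study". Neither dementia nor loss of capacity is an exclusion.
- **Target (Discussion):** "A special focus is put on the prevalence of dementia in this nursing home population". The Residents section counts Global Deterioration Scale stages 4 to 7 as dementia.
- **Size (Study design):** "A minimum of 500 residents per country are included into the study", with the reason "This number has been estimated as a representative sample, as the population of nursing homes is relatively homogenous compared to community dwelling populations".
- **Numbers included (Sampling procedure):** "In total, 644 residents are included in the Austrian sample", from seven consenting homes in a frame of homes with 60 to 120 residents. The Czech sample has 570 residents, in homes of 8 to 260 residents.
- **Data per home:** Table 1 and the Environmental factors section list the number of residents, or home size, among the variables collected for each home.
- **Limitations (Discussion):** the cross-sectional design, instruments not validated in Czech or German, and the use of proxy instruments. Selection through consent is not named.

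**The concern.** Entry requires a signature, and the ability to give one can fall with the condition being counted. The share with dementia among participants then estimates prevalence among residents who could be enrolled, which need not equal prevalence among residents of the homes. Enlarging the sample does not reduce such a bias. The homogeneity argument for 500 per country does not address it either, because it concerns how much residents vary and not which residents enrol.

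The prevalence figure is meant to inform policy makers on care planning. If enrolment by dementia status also differed between Austria and the Czech Republic, the planned country comparison would carry the difference. No listed data item or analysis would show or correct enrolment that depends on dementia.

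**Working it through.** **No figure of the plan to reproduce.** The article gives no assumed prevalence, precision or response rate behind 500 per country, and no enrolment rate by dementia status.

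**Inputs from the article**
- Austria: 644 residents included, 7 homes, 60 to 120 residents per home.
- Illustrative true prevalence *p*, from the Background: 67% (a Swedish study, cognitive impairment) and 89.8% (an Irish study, 58% diagnosed plus 31.8% testing in the possible range).

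**Assumptions:** 644 counts enrolled participants, and the seven homes lie within the frame's size range.

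**Step 1: participation floor.** The seven homes hold 7 × 60 = 420 to 7 × 120 = 840 residents. Overall participation is *c* ≥ 644/840 = 0.767. The mean of 644/7 = 92 participants per home also fits nearly complete participation.

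**Step 2: observed prevalence.** Let *c0* be the enrolment rate without dementia and *c1* the rate with dementia. Overall participation is *c* = *p·c1* + (1 − *p*)·*c0*, so the prevalence among participants is

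*o* = *p·c1*/*c* = 1 − (1 − *p*)·*c0*/*c*.

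The fall is greatest when *c* is at its floor and *c0* = 1. At *c* = 0.7667:

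| True *p* | Assumed *c0* | Observed *o* | Bias (points) |
|---|---|---|---|
| 67% | 0.80 | 1 − 0.264/0.7667 = 65.6% | −1.4 |
| 67% | 1.00 | 1 − 0.330/0.7667 = 57.0% | −10.0 |
| 89.8% | 0.80 | 1 − 0.0816/0.7667 = 89.4% | −0.4 |
| 89.8% | 1.00 | 1 − 0.102/0.7667 = 86.7% | −3.1 |

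At *p* = 67%, the implied *c1* is (0.7667 − 0.264)/0.67 = 75% in the first row and (0.7667 − 0.330)/0.67 = 65% in the second. If *c1* exceeds *c0*, the bias is upward: at 67%, a ratio *c1*/*c0* of 1.1 gives 69.1%, or +2.1 points.

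**Step 3: comparison with sampling error.** The simple 95% half-width, 1.96·√(*p*(1 − *p*)/*n*), at *n* = 644 is 3.6 points for 67% and 2.3 points for 89.8%. Clustering by home makes the true margins wider. The bias lies inside the simple margin at *c0* = 0.80 and outside it at *c0* = 1.00.

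**Step 4: worst-case bounds.** With no assumption about non-participants, true prevalence lies between *o·c* and *o·c* + (1 − *c*). For an observed 67% at the Austrian floor this is 0.67 × 0.7667 = 51.4% to 51.4% + 23.3% = 74.7%. Higher participation narrows the range.

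**Step 5: Czech Republic.** The text gives home sizes only as a range of 8 to 260, so no useful participation floor follows for the 570 residents.

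**The case against.** - **Signed consent is ordinary, and impaired residents are clearly meant to be studied.** This stands. Dementia is no exclusion, and the pain and behaviour scales include observational and staff-interview versions. A reader might infer that residents without capacity are shut out, or that only the resident may sign. The article says neither, and consent text was removed from the file. A representative route would weaken the mechanism, but the sample would still be selected by consent.
- **The direction is assumed.** This stands. Nothing in the article gives enrolment by dementia status.
- **A large bias is ruled out for Austria.** This largely stands. A reader might picture enrolment of 80% without dementia and 60% or 40% with it, which would turn a true 67% into 60% or 50%. Overall enrolment would then be 66.6% or 53.2%, and 644 participants would need about 967 or 1,210 residents. Seven homes hold at most 840. If 644 instead counts everyone living in the homes, it is a denominator and sets no participation floor.
- **A denominator exists.** This stands. Resident numbers per home are collected, so participation per home can be computed. The two selection figures are not shown, so an absent resident flow cannot be charged to the plan. A bare headcount does not, however, show whether non-participants have dementia more or less often.
- **Non-response handling belongs in a fuller analysis plan.** This is fair as to detail. What remains is that the entry rule as stated does not by itself deliver the population prevalence that the article names as its focus, and that the tally in the fix is best taken while the team is in each home.

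**Conclusion.** The point holds as a conditional risk of bias. Prevalence will be measured among enrolled residents and misstates prevalence among all residents of the homes if enrolment depends on dementia. Downward is the more likely direction, but this is a judgement that the documents do not establish.

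For Austria, at the 76.7% participation floor, the bias at a true 67% runs from about −1.4 points (80% enrolment without dementia) to −10 points (the extreme of complete enrolment without dementia). At a true 89.8% it runs from about −0.4 to −3.1 points. With higher participation, or equal enrolment by dementia status, it shrinks or vanishes. These figures require that 644 means participants and that the size range applies to the seven homes. The Czech bias cannot be bounded from the text.

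A reader might conclude that the headline figure is certainly too low or unusable. The documents do not support that. They support a limit on what the figure can claim until participation and selection are shown.

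**What to change.** 1. **Participation and bounds.** Use the resident numbers already collected to report participation for each home and country, with the worst-case bounds of Step 4. State who may sign.
2. **Aggregate tally.** During the planned month in each home, have the project assistant, who already supports chart review, supply an anonymous count of all permanent residents on one fixed day by recorded dementia diagnosis, age band and sex.
3. **Weighted estimate.** Beside the participant prevalence, report one weighted within home to that tally. Collapse sparse cells, keeping recorded diagnosis longest; the smallest Czech home has 8 residents.
4. **Wording.** If the two estimates differ, state the conclusion as prevalence among participating residents, and add consent-related selection to the limitations.

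**Cost:** one tally sheet per home from records already held, one weighting step, slightly wider intervals, and data-protection clearance for aggregate counts, which matters most in very small homes. Correction is only partial for undiagnosed non-participants. In the Irish study cited in the Background, 31.8 of the 89.8 percentage points, or 35%, had no diagnosis, so the bounds should be reported even when the two estimates agree.

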### Sampling procedure

#### Austria

The 137 nursing homes of Upper Austria (from a total of 886 nursing home in Austria) formed the basis for the Austrian randomized selection process (see Fig. 1)﻿. Nine homes had to be excluded from the study, because they were “under renovation”. The remaining Austrian sample of 128 nursing homes includes facilities with 60–120 residents. From the remaining 128 homes, 82 nursing homes are run by the federal state, 21 are under municipal administration and 25 are organized by the church or private organizations. Each nursing home was assigned an identification number (ID). All numbers were written on separate pieces of paper and folded, concealing the ID number. The folded papers where then placed in different bowls representing the three organisational categories. Taking the drop outs into consideration, 16 nursing homes were randomly selected in a stratified fashion from the bowls (50% federal state; 25% municipality, 25% church/private). With this method, 16 nursing homes (8 federal state homes, and 4 municipal homes and 4 privately run homes) were randomly drawn. Of these 16 homes, seven nursing homes (five nursing homes run by the federal state, one home run by municipality and one home run by the church) consented to participate. In total, 644 residents are included in the Austrian sample.

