#### Czech Republic

The 159 nursing homes (see Fig. 2) of Central Bohemia and the Prague region (from a total of 822 nursing homes in the Czech Republic) formed the basis for the Czech randomized selection process (100 homes of the category “homes for seniors” and 59 homes of the category “homes with a special regime”). Using a similar method as the Austrian team, 12 randomly selected homes were drawn (6 homes for seniors and 6 homes with a special regime) covering each sub-category (municipal, for-profit and non-profit). In the category “homes for seniors”, 6 nursing homes (3 municipal, 1 for-profit and 1 non-profit) consented to participate. In the category “homes with a special regime” four nursing homes (2 municipal, 1 for-profit and 1 non-profit) consented to participate. The resulting sample is very diverse in size – the smallest home provides services for 8 residents, whereas the biggest home provides care for 260 residents. In total, 570 residents are included in the Czech sample.

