### Statistical analysis plan and statistical considerations

The data will be exported from the database into CSV files via SQL-statements. Statistical analysis will then be performed via the open statistical software “R”. Descriptive statistics will be used to summarize the characteristics of the sample in the different countries and in the distinct nursing homes. A multilevel regression analysis will be performed per country to estimate the influence of different environmental and other factors (for example staffing) on the occurrence of neuropsychiatric symptoms. One particular issue will be the influence of the environments on the amount and severity of behavioural symptoms (e.g. the size of the nursing home, and patient/staff ratio). Another important issue will be the influence of the care team burden on the occurrence of behavioural problems. In addition, the correlation between the influence factors and the cognitive, functional und behaviour measurements will be investigated.

The distribution of the most important outcome variables and covariates will be used to check for outliers and differences between the two countries. Depending on the level of measurement Student’s *t*-test, Mann-Whitney *U* Test or *Chi*
^2^ Test will be used – especially for country comparison. Next, a pooled analysis will be performed and for the outcome variables, random effect models with the respective country as random factor will be conducted.

The statisticians of both project partners will cooperate on the definition of different topics of analysis.

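### Homes were drawn out of proportion to the frame and accepted unequally, yet only sample summaries are described, so an unweighted prevalence is not that of the frame, by a modest amount

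*Protocol article*

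**What the plan says.** Under Sampling procedure, Austria, the frame is broken down by organisational category: "82 nursing homes are run by the federal state, 21 are under municipal administration and 25 are organized by the church or private organizations". The draw used a different split: "16 nursing homes were randomly selected in a stratified fashion from the bowls (50% federal state; 25% municipality, 25% church/private"), that is, "8 federal state homes, and 4 municipal homes and 4 privately run homes". The homes that agreed were "five nursing homes run by the federal state, one home run by municipality and one home run by the church".

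Under Sampling procedure, Czech Republic, the frame is 100 seniors homes and 59 special-regime homes, and "12 randomly selected homes were drawn (6 homes for seniors and 6 homes with a special regime"). The draw is said to have covered municipal, for-profit and non-profit homes within each category. Six seniors homes are said to have agreed, but the bracketed breakdown is 3, 1 and 1. Four special-regime homes agreed.

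The section Statistical analysis plan and statistical considerations states: "Descriptive statistics will be used to summarize the characteristics of the sample in the different countries and in the distinct nursing homes". It adds t, Mann-Whitney or chi-square tests for country comparison, a multilevel regression per country for neuropsychiatric symptoms, and pooled models with country as random factor. It mentions neither sampling weights nor an adjustment for refusal. The Discussion puts particular emphasis on dementia prevalence, and Study design calls the planned number of residents representative.

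**The concern.** A disproportionate stratified draw is legitimate, but the homes then have unequal chances of selection. If refusal also differs by stratum, the participating homes form a third mix, which is neither that of the frame nor that of the draw. A plain proportion over the participants estimates prevalence in that third mix. Prevalence is the result meant to inform care planning, so readers will take it as the figure for the homes in the sampled regions. The size and direction of the shift depend on how the draw and the refusals combine and on whether prevalence differs between strata.

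**Working it through.** **The plan's own figures.** 137 − 9 = 128 = 82 + 21 + 25, and 16 × (0.50, 0.25, 0.25) = 8/4/4. Both reproduce. A proportional draw of 16 would have been 10.3/2.6/3.1 homes.

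**Shares and weights.** Draw fraction = drawn / frame; acceptance = participating / drawn; weight = frame / participating.

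| Stratum | Frame | Drawn | Participating | Draw fraction | Acceptance | Weight |
|---|---|---|---|---|---|---|
| Austria, federal state | 82 (64.1%) | 8 (50%) | 5 (71.4%) | 9.8% | 62.5% | 16.4 |
| Austria, municipal | 21 (16.4%) | 4 (25%) | 1 (14.3%) | 19.0% | 25% | 21 |
| Austria, church/private | 25 (19.5%) | 4 (25%) | 1 (14.3%) | 16.0% | 25% | 25 |
| Czech, seniors | 100 (62.9%) | 6 (50%) | 6 (60%), or 5 (55.6%) | 6.0% | 100%, or 83.3% | 16.7, or 20 |
| Czech, special regime | 59 (37.1%) | 6 (50%) | 4 (40%), or 4 (44.4%) | 10.2% | 66.7% | 14.75 |

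The Czech weights assume equal selection chances within each category. The article gives no frame counts for the sub-categories.

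**Shift in the raw figure.** With two groups, shift = (sample share − frame share) × gap in prevalence. The documents give no prevalence by stratum, so the gap is an assumption.

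- Austria, federal versus the rest, per 10-point gap: the draw alone gives (0.500 − 0.641) × 10 = −1.4 points; after refusal, (0.714 − 0.641) × 10 = +0.7 points. Refusal reverses the effect of the draw and halves its size.
- Czech Republic, special regime versus seniors, per 10-point gap: the draw alone gives (0.500 − 0.371) × 10 = 1.3 points; after refusal, (0.400 − 0.371) × 10 = 0.3 points, or (0.444 − 0.371) × 10 = 0.7 points with five seniors homes.
- Gaps of 20 and 30 points give 1.5 and 2.2 points in Austria, and 0.6 and 0.9 (or 1.5 and 2.2) points in the Czech Republic. A gap of zero gives zero.

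**Homes versus residents.** A resident prevalence depends on resident shares, which are not given by stratum for the sample or the frame. The Austrian frame "includes facilities with 60–120 residents", and "In total, 644 residents are included in the Austrian sample". If the two non-federal homes contributed between 60 and 120 residents each (assumption), the federal share of residents lies between (644 − 240)/644 = 62.7% and (644 − 120)/644 = 81.4%. Set against the 64.1% share of homes, the shift is −0.1 to +1.7 points per 10-point gap, so even its direction is open.

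**Cost in variance.** Kish factor for the Austrian home weights: n × Σw² / (Σw)² = 7 × (5 × 16.4² + 21² + 25²) / 128² = 7 × 2410.8 / 16384 = 1.03, an increase of about 3%.

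**The case against.** The strongest reply is that the article never says the analysis will be unweighted. Data management plan leaves the common quantitative analysis to a later step, and a full analysis plan that is not shown may contain weights. Strata are not wholly ignored either: organisational category is collected as an environmental factor, and descriptives per home are planned, from which stratum figures could be recovered. This stands as a limit. The point is that the article itself fixes a disproportionate draw, calls the sample size representative and, for prevalence, describes only sample summaries.

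The effect is also small beside sampling error. At an assumed prevalence of 70%, the Austrian 95% half-width is 1.96 × √(0.7 × 0.3 × [1 + 91 × ICC] / 644). That is about 5.9 points at ICC 0.02 and 11.2 at ICC 0.10 (both assumed). The difference in Austrian acceptance, 5/8 federal versus 2/8 other, is compatible with chance (Fisher p = 0.31). These facts bear on importance. They do not change the mix of homes being estimated.

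Three stronger readings are tempting, and the documents do not support them.

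- A reader might infer that unequal draw and unequal refusal compound. They work in opposite directions in both countries.
- A reader might infer that refusal by residents strengthens the case for weighting. The article gives no participation rate and nothing about non-participants. A rate of 80% in every home would give every resident the weight 1/0.80 = 1.25 and leave prevalence unchanged. Refusal related to dementia is not repaired by such weights.
- A reader might infer that weighting makes the country comparison like for like. Austria is stratified by operator and the Czech Republic first by type of home, so weighting restores each frame but leaves the two mixes different.

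**Conclusion.** The point holds in a limited form. Participating homes represent unequal numbers of frame homes, and the analysis as described does not take this into account, so an unweighted prevalence is not that of the sampled frame. By home shares the shift is about 0.7 points in Austria and 0.3 (or 0.7) points in the Czech Republic per 10-point gap between strata. This rests on an assumed gap, on home shares standing in for unknown resident shares, and on equal selection chances within each Czech category. The near-cancellation comes from which homes happened to agree and was not designed. Self-selection of homes within strata (9 of 16 Austrian homes did not take part) may well matter more, and weights do not correct it. The change is worthwhile because it is cheap, but the documents do not show a large bias.

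**What to change.** 1. Reconcile the Czech seniors count (six stated, 3 + 1 + 1 = 5). State whether the Czech sub-categories were drawing strata; if so, use their frame counts.
2. Report prevalence by drawing stratum in each country.
3. Add a frame-weighted estimate per country beside the raw one. Weight = frame homes / participating homes in the drawing stratum, times eligible / participating residents in the home, with clustering on home. Merge the two single-home Austrian strata for variance estimation, since neither gives a between-home variance alone.
4. Give home acceptance (7/16 in Austria; 10/12 or 9/12 in the Czech Republic) and resident participation with each prevalence.
5. State that weights do not correct refusal related to dementia or self-selection of homes within strata, and do not give the two countries the same stratum mix.

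The cost is survey-design code in R, which is already the planned software, a count of eligible residents per home, and about 3% more variance from the Austrian home weights. The weighted Austrian figure will lean on one home standing for 21 and another standing for 25, which is why it should complement the raw figure and not replace it.
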